#### Secondary outcomes

Fluid removal data aggregated over the duration of RRT, or the first 48 hours if shorter, will be calculated. Biochemical clearances and ventilator-free days while on RRT will be collected. Binary outcomes are: survival (to 30 days and to discharge), haemodynamic status, whether RRT was completed as intended, need for additional vascular access and unplanned change in dialysis circuit, exposure to blood transfusion, bleeding from insertion line and anticoagulant use.

Responses to questionnaires (1) parent/guardian about their experience and (2) to staff regarding acceptability and usability.

### Planned analysis

Analysis of all available data will be on the basis of intention-to-treat. A subgroup analysis will compare NIDUS with conventional CVVH that is, excluding PD. For the latter group the amount of fluid removed (*X*) will be compared with the amount the machine reports to have been removed (*A*).

The primary outcome will be analysed using a linear model with fixed effects for treatment, period and cluster. The use of a fixed rather than random effect for cluster is a response to the interruptions to data collection due to the effect of COVID-19 on PICUs and the subsequent difficulty in defining a suitable dispersion structure. Sensitivity analyses will use a generalised estimating equation and will assess the assumptions about *X*. If these are untenable then *X-A* will be modelled directly, with treatment dependent variances for the error terms. The above linear model will be applied to the non-binary secondary outcomes. Binary outcomes will be analysed using generalised mixed models if possible but using simple tabulations if more sophisticated analyse are infeasible. Questionnaire data will be tabulated by treatment.

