### Current RRT

PD is used frequently to support infants after open heart surgery.^5 13^ PD is technically simpler than HD; there is no lower size limit but complications are common in the smallest patients.^4^ UF is unpredictable, and chemical clearance less efficient, especially in unstable babies who develop splanchnic vasoconstriction and who also risk developing necrotising enterocolitis. This renders PD impossible, as does abdominal surgery and congenital abdominal wall defects. Larger critically ill infants with multiorgan failure are often treated with a variety of continuously delivered HD modalities (CRRT).^4 5 9^ Vascular access for HD modalities including continuous veno-venous haemofiltration (CVVH) is problematic as the size of central venous line required for adequate blood flow is disproportionately large for the size of the baby especially when a double lumen line is needed.

While there are no randomised controlled trials in infants, publications indicate recurring themes of difficulties with vascular access and blood flows, fluid balance, rapid clotting, loss of circuits and hypotensive episodes at initiation.^6–9^

Conventional HD and CRRT machines in the UK are used in PICU unlicensed as they are CE marked for use in adults and bigger children. Manufacturers quote fluid balance control as ±30 mL/hour,^14^ and they, therefore, are not licensed for babies weighing <8 kg (or approved for use in children of <20 kg in the USA). The recommended minimum 7-French, dual-lumen vascular access lines and continuous 40 mL/min blood flows are difficult to achieve in the smallest babies. Their relatively large circuit volume (50–70 mL) produces sudden dilution of blood on commencing treatment if crystalloid primed, and increases the risk of anaemia with circuit loss. Hypotension on connection is a reported problem.^6 15 16^ Blood priming risks exposing the baby abruptly to aberrant chemical and pH changes, which are reduced by predialysing the circuit.^17^ Exposure to blood transfusions increases the risk of developing tissue-type sensitisation which may be important if renal function does not recover and renal or other solid organ transplant is considered in the future.

There is one CE marked new device for smaller children, the CARPEDIEM, which is not yet available in the UK to enable comparisons,^18 19^ others, notably in USA, have adapted other adult devices like Aquadex.^9 20^

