### NIDUS technology

In 1995, a group in Newcastle designed a novel HD circuit, which operated by different principles that is, by syringes, and uncoupled the baby’s blood flow capacity from the requirements of the dialysis filter.^21^ In 2005, they reported the results of automating this as a miniaturised machine (circuit volume less than 10 mL), with which four babies weighing under 4 kg were treated, using a single-lumen access line, and without the need for blood priming.^22^ This device was subsequently developed into NIDUS,^3^ which is used as the intervention device in the I-KID study. This clinical investigation will contribute to the current knowledge base and further understanding of the effects of RRT and address the need for improved technology to provide RRT effectively and safely for small babies.^1 23 24^

Safety monitoring is an important focus of this study. The NIDUS makes a downloadable constant recording of all activity data including volumes, flows, pressures, alarms and response to alarms so any alarm or event, however small, can be subsequently analysed. The NIDUS potentially provides a safer way of performing RRT on babies by using a novel circuit that allows precise ultrafiltrate control thus reducing the potential for errors in ultrafiltrate removal that would be trivial for larger children but are not for a baby. Its small circuit volume (<10 mL) potentially avoids the need for blood priming with stored blood which has associated immediate risks and long-term risks of developing sensitising antibodies.

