### Statistical considerations

#### Primary outcome

The primary aim is to compare the precision of the standard therapy and NIDUS to deliver the fluid removal rate prescribed by the treating physician. The primary outcome is based on the first available determination of fluid removal over a period exceeding 1 hour and within the first 48 hours of commencement of RRT: if the observed removal is *X* and the prescribed removal is *A*, the primary outcome is log|*X-A*|. The expected difference of this quantity between the treatment groups is the log of the ratio of the SDs of the determinations by the two methods. The method supposes that *X* follows a normal distribution with mean *A* and hence the variance of the outcome is 
$\pi^{2}/8$
.

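### The NIDUS-versus-CVVH subgroup is not like for like as written: the reference value A changes, possibly for CVVH only, and dropping PD removes babies from the control side alone

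*Protocol article*

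**What the plan says.** All references are to the protocol article.

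- **Primary outcome.** The aim is to compare how precisely the two therapies are able "to deliver the fluid removal rate prescribed by the treating physician". X is observed removal, A is prescribed removal, and the outcome is log|X−A|.
- **Planned analysis.** "A subgroup analysis will compare NIDUS with conventional CVVH that is, excluding PD". The following sentence begins "For the latter group the amount of fluid removed" and says that this X will be "compared with the amount the machine reports to have been removed". That machine-reported amount is again called A.
- **Table 1 and Study design.** Control is PD or CVVH. NIDUS is the only therapy of the intervention periods.
- **Current RRT.** PD is described as common after open heart surgery. Of continuous therapy the section says: "Larger critically ill infants with multiorgan failure are often treated with a variety of continuously delivered HD modalities (CRRT".
- **NIDUS technology.** The device "makes a downloadable constant recording of all activity data including volumes, flows, pressures" and other items, so a machine-reported volume should exist for NIDUS as well.

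**The concern.** This is the only machine-against-machine comparison that the article plans, and many readers will look to it. Two features prevent it from isolating a device effect.

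First, the last group named before *the latter group* is conventional CVVH, and nothing says that NIDUS changes reference too. On that reading CVVH is judged by how well its meter agrees with the weighed fluid. NIDUS is judged by how well the prescription was delivered, which also includes any gap between what the machine ran and what was ordered.

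Second, PD exists only in control, so excluding it filters one arm by a clinical choice. Intervention-period babies pass no such filter. Randomising centres to sequences does not protect a contrast defined this way.

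**Working it through.** The article gives no figure for this subgroup, so there is none to reproduce. The check follows the article's definitions through its own model and uses the design ratio of 3 (Sample size) as a yardstick.

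**Inputs from the article.** X is normal with mean A, and the expected treatment difference in log|X−A| is the log ratio of the SDs (Primary outcome). Treatment, period and cluster are all fixed effects (Planned analysis).

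**Assumed inputs, not in the article.** The ratio d/m of two error components, the share p of NIDUS babies who would have had PD, and the factor k by which their error SD differs from that of CVVH-type babies.

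**Step 1: how errors of definition pass through.** Under the model, E log|X−A| = log SD + a constant that is the same in both arms. Multiplying one arm's error SD by f therefore multiplies the reported SD ratio by f (CVVH) or 1/f (NIDUS).

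**Step 2: reference changed for CVVH only.** Let the CVVH error against prescription be the sum of two independent parts: machine versus prescription (SD d) and true versus machine (SD m). Against prescription the SD is √(d²+m²); against the machine reading it is m. The CVVH/NIDUS ratio is multiplied by m/√(d²+m²).

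| d/m | Factor = ratio shown by identical devices | True ratio of 3 appears as |
|---|---|---|
| 0.5 | 1/√1.25 = 0.89 | 2.68 |
| 1 | 1/√2 = 0.71 | 2.12 |
| 2 | 1/√5 = 0.45 | 1.34 |

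If both arms use the machine reading, this factor disappears. The contrast is then a ratio of metering errors, which is not the delivery question of the primary outcome.

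**Step 3: PD excluded from control only.** Let CVVH-type babies have error SD s and PD-type babies ks, on any device. The mean log SD is log s in the CVVH group and log s + p·log k in the NIDUS group. The ratio is multiplied by k^(−p).

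| p | k = 0.5 | k = 2 |
|---|---|---|
| 0.25 | 1.19 | 0.84 |
| 0.50 | 1.41 | 0.71 |
| 0.75 | 1.68 | 0.59 |

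Within each centre the control periods supply CVVH babies only and the intervention periods supply all babies. The case-mix difference therefore moves with treatment, and the period and cluster terms do not remove it.

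**Step 4: both together.** The factors multiply. With d/m = 1 and p = 0.5, k = 0.5 gives 0.707 × 1.414 = 1.00, while k = 2 gives 0.707 × 0.707 = 0.50. The two effects can cancel or compound, so no net direction follows.

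**The case against.** **The wording may mean both machines.** *The latter group* can be read as the NIDUS-plus-CVVH subgroup, set against the analysis of all data just before it. The content supports this: both are machines, NIDUS logs volumes, and removal is obtained from weighed bags (Sample selection and outcomes), so weighed against reported volume is a coherent metering question. This stands. A mismatch of reference between arms is therefore conditional on the literal reading. What remains on the other reading is an unannounced change of question under the same symbol.

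**The case-mix sizes are assumed.** A reader might infer that, because continuous therapy goes to larger infants and error grows with weight, the subgroup must favour NIDUS. The article does not support that. It gives no weights by modality, and its one error figure is an absolute volume (±30 mL/hour, Current RRT). Its remarks on who receives PD or CRRT are general background, not data from the six sites. This objection removes any claim about size or direction, but not the one-sided exclusion.

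**It is a subgroup, and details may sit in the full protocol or SAP.** Lack of adjustment in a condensed article is indeed no fault in itself. The point rests on what the article does state: two meanings of A, and an exclusion that can act on one arm only.

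**Conclusion.** The point holds in conditional form. The change of reference biases the contrast only if *the latter group* means CVVH alone; otherwise it is an ambiguity and a change of question that needs stating. The one-sided removal of PD babies holds on either reading and leaves a comparison that randomisation does not protect.

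The size and direction of any bias cannot be computed from the document. The ranges of 0.45 to 0.89 (reference) and 0.59 to 1.68 (case-mix) rest on assumed d/m of 0.5 to 2, p of 0.25 to 0.75 and k of 0.5 to 2. They show only that a distortion could be material beside a design ratio of 3.

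A reader might go further and infer that the trial's main result is compromised. It is not: the primary comparison keeps PD and CVVH in control and uses prescribed removal in both arms.

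**What to change.** 1. State that A has the same definition in both arms of this subgroup. Give one version with machine-reported removal for both (NIDUS from its activity log) and one with prescribed removal for both, under distinct symbols. Say that the first addresses metering and the second delivery.
2. Add log body weight to the subgroup model and, where recorded, post-cardiac-surgery status.
3. Report the subgroup as a non-randomised comparison.
4. Optionally, for NIDUS babies still to be enrolled, record which conventional modality would have been used, for a sensitivity analysis only. This is an unblinded counterfactual judgement and cannot be collected prospectively for babies already treated, so it should not define the main subgroup.

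If the full protocol or SAP already settles any of this, the article's wording need only be aligned with it.

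**Cost:** a few sentences, a second run of one model, and one or two extra parameters in a subgroup that is already small. Planned recruitment is (3×14 + 9 + 9 + 3) × 1.5 = 94.5 babies. If half of the control babies had CVVH (an assumption), about 70 to 72 remain, depending on where the small centres fall in the sequences. Adjustment reduces the case-mix bias from the measured factors but cannot remove it all.

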### Study design

The study uses a cluster randomised standard stepped-wedge (SW) design^25^ with four periods and three sequences (figure 1). The control periods use conventional therapy (PD or CVVH), with NIDUS used in intervention periods. Each site will be trained in setting up and using the NIDUS before switching to an intervention period. The design means that all participating centres will have the chance to use both treatments during the course of the study. PICU nurses will need to be competency assessed before each site can begin using the intervention; 24 hours on call nurse/clinician is provided from Newcastle for telephone support. Using an SW design permits the phased training on NIDUS and allows within-centre comparisons to contribute to the treatment estimate.

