### Randomisation

Past records suggested that Great Ormond Street Hospital, Evelina and Southampton (the large centres) treat substantially more patients for RRT than Birmingham, Bristol and Newcastle (the small centres). To avoid large imbalances between the sequences, random permutation in R software was used to allocate one large and one small centre to each sequence. The statistician was blind to the identities of the centres during the allocation.

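### The unadjusted fallback for binary secondary outcomes would, read as tables by treatment, confound NIDUS with calendar period and partly with centre

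*Protocol article*

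**What the plan says.** The Secondary outcomes section of the protocol article lists the outcomes concerned: "Binary outcomes are: survival (to 30 days and to discharge), haemodynamic status, whether RRT was completed as intended". Additional vascular access, unplanned circuit change, transfusion, bleeding and anticoagulant use follow in the same list.

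The Planned analysis section then sets a two-step rule. "Binary outcomes will be analysed using generalised mixed models if possible" is the first step, and the second is "using simple tabulations if more sophisticated analyse are infeasible". It does not say what counts as infeasible, or whether the tables are split by centre or period.

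The same section analyses the primary outcome "using a linear model with fixed effects for treatment, period and cluster" and applies that model to the non-binary secondary outcomes. It explains the fixed cluster effect by the COVID-19 interruptions and the "subsequent difficulty in defining a suitable dispersion structure".

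The design has "four periods and three sequences" (Study design), and the randomisation was made to "allocate one large and one small centre to each sequence" (Randomisation).

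**The concern.** In a stepped wedge, treatment and calendar time are tied together by design. Every centre starts on control and ends on NIDUS, and centres that cross early contribute more NIDUS babies than centres that cross late. An estimate of the device effect therefore needs adjustment for period and centre. The plan provides this for the primary and non-binary outcomes, but the last resort for binary outcomes has none.

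The step down is also larger than it needs to be. If a mixed model cannot be fitted, the fixed-effects specification used for the primary outcome is still available, yet the rule passes over it.

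At stake is whether a difference in transfusion, circuit changes, bleeding, completion of RRT or survival reflects the device or reflects when and where the babies were treated. Time effects are plausible here: the Recruitment section reports three pauses, a temporary regulatory withdrawal and the COVID-19 stop.

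**Working it through.** **Inputs.** Four periods, three sequences (Study design). One large and one small centre per sequence (Randomisation). Annual recruitment of 14 in each of three large centres, 9 in each of two small centres and 3 in Newcastle, with periods of 4.5 months (Sample size). I take the usual layout, in which the sequences cross after periods 1, 2 and 3; the design figure is not shown.

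**The plan's own figure.** (3×14 + 2×9 + 3) × 1.5 years = 63 × 1.5 = 94.5, which agrees with the stated 95.

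**Mean period, sequences weighted equally.**
- Control: (3×1 + 2×2 + 1×3)/6 = 1.67
- NIDUS: (1×2 + 2×3 + 3×4)/6 = 3.33
- Gap: 1.67 periods, or 1.67 × 4.5 = 7.5 months as planned

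**Mean period, weighted by recruitment.** Expected babies per centre and period are 14×0.375 = 5.25, 9×0.375 = 3.375 and 3×0.375 = 1.125. With Newcastle in the middle sequence, the sequence totals per period are 8.625, 6.375 and 8.625.
- NIDUS: (2×8.625 + 3×15 + 4×23.625)/47.25 = 3.32
- Control: (1×23.625 + 2×15 + 3×8.625)/47.25 = 1.68
- Gap: 1.63

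The article does not say which sequence Newcastle is in. Placing it first or last gives 3.30 against 1.62, or 3.38 against 1.70, a gap of 1.69. Across placements, period 1 holds 48–53% of controls and no NIDUS babies; period 4 holds 48–53% of NIDUS babies and no controls.

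**Centre.** With Newcastle in the middle, the first-crossing sequence supplies 3×8.625/47.25 = 55% of NIDUS babies and 8.625/47.25 = 18% of controls. The last-crossing sequence is the reverse. Across placements the ranges are 43–55% and 13–19%. Every centre contributes to both conditions, so this confounding is partial.

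**Spurious crude difference with no device effect.** This is the drift per period times the gap.

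| Assumed drift | Crude difference |
|---|---|
| 5 points per period | 5×1.63 to 5×1.69 = 8.2 to 8.4 points |
| 5 points over the whole trial | about 3 points |
| 10 points over the whole trial | 5 to 6 points |
| 20 points over the whole trial | about 11 points |

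A 20-point difference in survival between first- and last-crossing centres, with no drift, gives 6 to 7 points.

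**With the primary model's fixed effects.** A drift common to all centres is absorbed by the period terms, so the expected treatment estimate is 0. In sets of 2,000 simulated trials with risk starting at 40% and falling 5 points per period, a Fisher test on the crude table rejected in about 8–11%. The fixed-effects linear model with HC3 standard errors rejected in about 3.5–4.6%.

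**Precision.** The standard deviation of the adjusted risk difference is about 0.19, so a 95% interval is about ±1.96×0.19 = ±0.37. The crude difference has about 0.10, or ±0.20.

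**How readily the fallback is reached.** A logistic model with treatment, period and a random centre intercept (assumed standard deviation 0.4 on the logit scale) was fitted to 300 simulated trials per scenario at the planned sizes. Estimates diverged in about 1% of trials at a risk of 30–40%, 13% at 15% and 78% at 5%. The Background section puts mortality at up to 20–40%. The Recruitment section reports 62 controls, which leaves at most 95 − 62 = 33 NIDUS babies if the total stays at 95. These rates are therefore indicative only.

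**The case against.** The strongest reply is that mixed models come first and tables apply only when more sophisticated analyses are infeasible. Taken literally, that condition is not met while a fixed-effects or penalised model can be fitted. No layout, test or effect claim is attached to the tables, and such details may be settled in an SAP or full protocol not shown here. The adjusted estimate is also so imprecise that, under the 5-point drift, its root mean squared error exceeds that of the crude difference (0.185 against 0.124).

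Part of this stands. The fallback is conditional, the layout by treatment is a reading, the drift is assumed, and adjustment is costly. But the two-step rule is stated text and names no adjusted alternative. It says the outcomes are analysed this way, and the next sentence tabulates the questionnaires by treatment, which supports that reading. A smaller error for a biased estimate depends on the drift assumed and does not make its interval valid.

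Three stronger inferences are tempting but unsupported.
- **That the fallback is likely, survival included.** The article reports difficulty in choosing a dispersion structure after the interruptions, not that a random effect cannot be fitted. At the mortality it cites, the simulated mixed model seldom failed.
- **That the table largely compares babies before and after the COVID-19 shutdown.** The Recruitment section gives no such split, and its 2019 pauses for device problems point to NIDUS use before the shutdown.
- **That any secular change would be read as a device effect.** This depends on the size of the change, the table layout and whether any between-treatment claim is made.

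**Conclusion.** The point holds as a conditional weakness in the analysis of secondary outcomes. If the fallback is used and the tables are by treatment, the comparison is confounded with period and, partly, with centre. The gap in mean period of 1.63 to 1.69 follows from the planned design and recruitment. The figure of about 8 points also needs the assumed drift of 5 points per period; smaller trends give proportionately smaller differences. Sparse outcomes, possibly bleeding, are the most exposed, and survival less so. The primary outcome is not affected. The rule should be changed before analysis, because the plan already contains the adjustment that is needed.

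**What to change.** Keep the mixed model as the first step if wished, but replace the fallback. State that, where it cannot be fitted, each binary outcome will be analysed with fixed effects for treatment, period and cluster, as for the primary outcome:
- a linear probability model giving a risk difference with HC3 standard errors, with model-based errors named as the alternative where HC3 is undefined (for example when a centre contributes a single baby);
- Firth-penalised logistic regression where events are sparse.

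State that tabulations are descriptive, shown by centre and period, and that no between-treatment inference is drawn from them.

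This changes analysis wording only; no further data are needed. The cost is precision: 95% intervals of about ±37 points at the planned size, against about ±20 for a crude comparison. The plan should say so, so that a wide adjusted interval is not taken as evidence of no difference.
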